### Definitions

Culture of *M. tuberculosis* will be considered to be converted to negative when two or more consecutive cultures, taken at different visits, are found to be negative in liquid medium. When a participant cannot produce sputum after the first negative culture sputum, they will be considered as having achieved culture conversion. The submission date of the first confirmed negative sputum culture will be regarded as the date of culture conversion. If *M. tuberculosis* is found to be re-cultured two or more times following a negative culture conversion, this will be termed culture reversion [18]. Treatment success is defined as achieving negative culture conversion and maintaining negative cultures till the end of treatment.

The sum of treatment failure, recurrence, death during treatment (except for accidents and suicide), loss to follow-up, and withdrawal from the study will be designated as “unfavorable outcomes.” Treatment failure will be defined as participants who fail to achieve culture conversion during treatment period, or as participants using second-line anti-TB drugs for more than 4 weeks. Recurrence will be assigned to participants that indicate the presence of *M. tuberculosis* in sputum cultures for two or more times after the end of treatment.

Adverse events will be defined when undesirable medical events have occurred in participants, irrespective of a causal relationship with the treatment [19]. When adverse events result in death, life-threatening conditions, patient hospitalization or prolongation of existing hospitalization, persistent or significant disability or incapacity, or a congenital anomaly or birth defect, the events will be classified as serious adverse events. The severity of each adverse event will be assessed based on Common Terminology Criteria for Adverse Events (CTCAE) version 5.0 [20].

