### Study outcomes

The primary outcome is the proportion of unfavorable outcomes at 18 months after randomization.

Secondary outcomes include time to unfavorable treatment outcomes, time to culture conversion on liquid medium, treatment success rate at the end of treatment, proportion of recurrence at 18 months after randomization, time to recurrence after treatment completion, and adverse events of grade 3 or higher during treatment.

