### Sample size calculation

The objective of this study is to determine whether the new regimen is non-inferior to the existing standard treatment. The primary outcome is an unfavorable treatment outcome at 18 months after randomization. Based on the existing study [21], a 10% unfavorable treatment outcome for the standard treatment (control group) and a 0% difference from the investigational group is assumed. To obtain a study with 80% power and a 2.5% one-sided significance level for the non-inferiority recognition limit of 6%, each group will contain 393 participants. Assuming a 15% dropout rate [22], the total number of study participants will be 926, resulting in 463 participants in each group. In the occurrence of participant withdrawal within 7 days of randomization, replacement participants may be recruited.

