### Statistical analysis

The results of this trial for outcomes will be analyzed based on intention-to-treat (ITT), modified ITT (mITT), and per protocol (PP) approaches, with a primary consideration for mITT results. The ITT group will include all participants who are randomized after satisfying eligibility criteria. The mITT group will include participants who are randomized and who have received the study drugs at least once. The PP group will include participants in the mITT group who have completed the standard treatment for at least 20 of the 24 weeks for the control group or those who have completed the planned treatment for at least 10 of the 12 weeks for the investigational group. A safety analysis will be performed based on the safety group, which will include participants who have been administered with at least one dose of the investigational drugs.

For the primary outcome analysis, the frequency of occurrence of unfavorable outcomes in the control and investigational groups will be analyzed, and the incidence rate of unfavorable outcomes ($${\widehat{P}}_{T}, {\widehat{P}}_{C}$$) and the 95% confidence interval will be estimated. In this non-inferiority test, if the upper limit of the two-sided 95% confidence interval of the difference in incidence of unfavorable outcomes at 18 months between the investigational and control groups ($${\widehat{P}}_{T}-{\widehat{P}}_{C}$$) is less than 6%, it will be concluded that the investigational group is not inferior to the control group.

For the analysis of time to unfavorable outcome, time to culture conversion, and time to recurrence, the median time of each group will be estimated using the Kaplan–Meier method and will be compared with the log-rank test. Treatment success rate and recurrent rate at the end of treatment will be compared with the chi-square test or Fisher’s exact test between the two groups.

Safety will be assessed based on the occurrence of adverse events during the clinical trial period. The frequency and proportion of all adverse events, serious adverse events, and adverse events of grade 3 or higher will be summarized and compared using the chi-square test or Fisher’s exact test.

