## Discussion

The Hi-DoRi-3 is a phase 3 open-label, multicenter, randomized, non-inferiority clinical trial that aims to investigate the effectiveness of a high-dose rifampicin-containing regimen for the treatment of drug-sensitive TB. In this study, the effectiveness and safety of a regimen with a shortened and individualized treatment duration will be compared with the standard 6-month regimen for TB treatment. The three-drug intervention regimen will include high-dose rifampicin (30 mg/kg) with isoniazid and pyrazinamide, which will be administered until culture conversion, followed by 12-week administration of high-dose rifampicin and isoniazid.

In South Korea, the treatment success rate of TB is ~ 90%. While less than 1% of TB patients could not be cured, 5.3–25.2% of TB patients were lost to follow-up [23]. The standard 6-month regimen, comprising four drugs, has remained unchanged for almost 40 years [3]. To enhance compliance and adherence to TB treatment, simple, less toxic, and shorter regimens are needed. With the aim to shorten treatment duration in TB patients, 4-month fluoroquinolone-containing regimens were compared with the standard treatment [7–9]; however, non-inferiority of these regimens was not proven.

For the last ~ 40 years, recommendations for the maximal dose of rifampicin have been confined to 10 mg/kg or 600 mg per day [4, 17]. The peak concentration after ingestion of the currently recommended dose of rifampicin is considered to be well above the minimum inhibitory concentration of *M. tuberculosis* [13]. However, this dose is at the lower end of the dose–response curve, and the drug concentration in *M. tuberculosis* and at the site of infection has not been considered [13]. Increased rifampicin exposure led to higher bactericidal and sterilizing activity for TB according to several in vitro and in vivo studies [24–26]. In human studies, higher doses of rifampicin shortened the time to sputum culture conversion compared with the conventional rifampicin dose [12, 14, 27]. The rate of serious adverse events in patients receiving higher doses of rifampicin was comparable to that in patients receiving the conventional dose [16].

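### The recurrence comparison is tied to the wrong time point, and a crude chi-square test on the mITT set would by default count participants lost before relapse could be seen as non-recurrent

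*Protocol article*

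**What the plan says.** All references are to the protocol article.

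- **Outcome.** Study outcomes lists two secondary recurrence outcomes: "proportion of recurrence at 18 months after randomization, time to recurrence after treatment completion".
- **Test of the proportion.** Statistical analysis: "Treatment success rate and recurrent rate at the end of treatment will be compared with the chi-square test", with Fisher's exact test as the alternative.
- **Time-to-event analysis.** The same section covers "time to culture conversion, and time to recurrence, the median time of each group will be estimated using the Kaplan–Meier method", with a log-rank comparison.
- **Definition.** Under Definitions, recurrence needs "presence of *M. tuberculosis* in sputum cultures for two or more times after the end of treatment". Loss to follow-up and withdrawal are components of the unfavorable outcome. No recurrence status is given for a participant who leaves before the criterion can be met.
- **Analysis sets.** Statistical analysis applies ITT, mITT and PP to the outcomes and gives mITT (randomized, at least one dose) priority. No separate set is named for recurrence.
- **Dropout.** Sample size calculation: "Assuming a 15% dropout rate", with no timing and no split by arm.

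**The concern.** There are two linked problems in one sentence.

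First, the sentence places the recurrence rate at the end of treatment. By definition no recurrence can have occurred by then, and the outcome list says 18 months after randomization. Taken literally, the test compares two zeros.

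Second, once the time point is corrected, a binary test on the mITT set needs a yes or no for every participant. Someone who leaves before two positive post-treatment cultures cannot meet the definition and falls into the non-recurrent group by default. The planned Kaplan–Meier analysis does not fill the gap. It promises a median, which is not reached unless about half the participants relapse, and a log-rank test. Its clock starts at treatment completion. The crude proportion is therefore the only 18-month recurrence risk that the article fixes.

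Relapse is the natural risk of a shortened regimen. The primary composite adds relapse to loss and withdrawal, so fewer losses could offset more relapses within it. The separate recurrence outcome is where such an offset would show.

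**Working it through.** **Time point.** Three statements side by side:

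| Section | Time attached to recurrence |
|---|---|
| Study outcomes | 18 months after randomization |
| Definitions | only after the end of treatment |
| Statistical analysis | at the end of treatment |

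The third cannot be reconciled with the first two.

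**The plan's own figures.** Only the primary outcome has a sample size. With 10% in both arms, a 6% margin, one-sided 2.5% and 80% power:

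- n = (1.960 + 0.842)² × (0.10 × 0.90 + 0.10 × 0.90) / 0.06² = 392.44, so 393 per arm.
- 393 / 0.85 = 462.35, so 463 per arm and 926 in total.

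These reproduce exactly, and nothing below changes them.

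**Size of the understatement.** The article gives no expected recurrence risk, so p is assumed. Let f be the share of the dropouts' recurrences that are seen before they leave (also assumed), and let dropout be unrelated to relapse. With 15% dropout and dropouts kept in the denominator as non-recurrent:

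observed risk = p × (0.85 + 0.15 × f)

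| f | p = 5% reads as | relative understatement |
|---|---|---|
| 0 | 5% × 0.85 = 4.25% | 15% |
| 0.5 | 5% × 0.925 = 4.62% | 7.5% |
| 0.8 | 5% × 0.97 = 4.85% | 3% |

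For p from 2% to 10%, the largest shortfall (f = 0) is 0.15 × p, which is 0.3 to 1.5 percentage points.

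**Arm difference** (f = 0; true risks assumed at 3% control and 8% investigational, a 5-point excess):

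- 15% loss in both arms: 0.85 × (8 − 3) = 4.25 points.
- 15% loss investigational, 8% control: 8 × 0.85 − 3 × 0.92 = 6.80 − 2.76 = 4.04 points.
- 8% loss investigational, 15% control: 8 × 0.92 − 3 × 0.85 = 7.36 − 2.55 = 4.81 points.

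With a true 5% in both arms and assumed losses of 20% and 10%, the arms read 5 × 0.80 = 4.0% and 5 × 0.90 = 4.5%. The arm that loses more looks better, whichever arm it is.

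**Power** for 3% versus 8%: 0.917 with all 463 per arm observed, 0.866 with dropouts scored as non-recurrent, 0.869 with 393 completers per arm. Almost all the power lost comes from the missing observations, so the scoring problem is one of bias.

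**What censoring does.** In the f = 0 case the 85% still under observation contribute 4.25 / 0.85 = 5%, which recovers the assumed risk. The per-arm standard error goes from √(0.0425 × 0.9575 / 463) = 0.94 points to √(0.05 × 0.95 / 393) = 1.10 points.

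**The case against.** The strongest reply is that the article never says dropouts count as recurrence-free. The denominator could be all mITT participants, treatment completers, or those assessed at 18 months, and missing-data rules for a secondary outcome are commonly left to an analysis plan that is not shown here. This stands to the extent that the scoring is an inference. It does not remove the point. The article fixes a crude test, applies the mITT set to outcomes without an exception for recurrence, and plans no other estimate of 18-month risk.

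It can also be said that the time-to-recurrence analysis accommodates incomplete follow-up. It can, although no censoring rule is stated. As described, it yields a median and a p-value but no 18-month risk.

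Several stronger readings are tempting and are not supported:

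- **That non-inferiority is compromised.** Loss and withdrawal count as unfavorable in the primary outcome, so that conclusion is untouched.
- **That 15% of participants will have unseen relapses.** The 15% is a sample-size allowance without timing. Some participants will leave after their relapse has been seen, and those lost during treatment are not yet at risk of recurrence as defined. It is an upper bound.
- **That the trial expects losses as far apart as 5.3% and 25.2%.** The Discussion's statement that "5.3–25.2% of TB patients were lost to follow-up" is background for South Korea, not an assumption for either arm.
- **That the bias favors the new regimen.** If the shorter regimen reduces loss, as intended, heavier loss in the control arm would flatter control.

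Deaths are not part of the complaint, because a participant who dies remains non-recurrent under the competing-event approach as well.

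**Conclusion.** The time point in the Statistical analysis sentence is wrong on the article's own terms. That part needs no assumption.

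The crude chi-square or Fisher comparison is a weak choice for the corrected 18-month outcome. Under the stated definition and a literal mITT denominator, it understates each arm's recurrence by up to 15% in relative terms, or about 3% to 7.5% if 80% to half of the dropouts' recurrences are seen first. At an assumed 5% risk this is at most 0.75 points per arm. Equal loss shrinks a true difference by the same factor; unequal loss can shift it either way. These sizes rest on assumed recurrence risks, on the planned 15% dropout, and on dropout being unrelated to relapse.

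The matter concerns a secondary outcome. It should be corrected because the remedy is cheap and this outcome isolates relapse, but neither the sample size nor the primary conclusion changes.

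**What to change.** 1. In Statistical analysis, separate the two outcomes: treatment success at the end of treatment, and recurrence at 18 months after randomization.
2. Replace the crude chi-square or Fisher comparison of recurrence with the cumulative incidence of recurrence at 18 months from randomization, by arm, in the mITT set. Censor lost or withdrawn participants at their last culture assessment, and treat death and treatment failure as competing events. Report the arm difference with a 95% confidence interval.
3. Keep the crude count of recurrences by arm as description, with its denominator stated.

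The cost is wording and a little programming. Tables 3 and 4 already schedule cultures at every follow-up visit, so no new assessments are needed; the article does not show whether every date required is captured in the database. The statistical price is a slightly wider interval and the assumption that censoring is non-informative.

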### Data collection and management

This study will use a web-based electronic case report form (e-CRF) with Research Electronic Data Capture (REDCap) constructed by the MRCC in collaboration with an outsourced contractor. The e-CRF designed for this study will use dummy variables for user acceptance testing to confirm its validity. During the study, medical personnel not participating in the study will monitor the trial. These personnel will visit study sites to monitor all aspects of the trial, including adherence to the protocol in accordance with Good Clinical Practice, study participant protection, and data accuracy of the study.

### Supervision of the trial

A Data and Safety Monitoring Board (DSMB), composed of two respiratory specialists who have experience treating TB patients and one statistician from another institute with no conflict of interests, will review data every 3 months during the trial. The DSMB could provide recommendations for protocol changes (including advice on continuation or cessation) based on the results.

### Confidentiality

The collection and operation of participant personal information in this study is limited to the data necessary for the efficacy, safety, and tolerability testing of the study drug. Data will be carefully collected and operated to comply with relevant data confidentiality laws and regulations and to ensure confidentiality. Paper files containing participant data (including personally identifiable information and copies of signed consent forms) will be securely stored in a locked office on site in locked filing cabinets. Digital files containing participant data will be stored as password-protected files on university-maintained servers. Access to study files will be restricted to authorized personnel only. The items in the present study protocol comply with the Standard Protocol Items: Recommendations for Interventional Trials (SPIRIT) checklist (see Additional file 1).

### Provisions for post-trial care

Participants with recurrence will receive standard TB treatment in accordance with guidelines.

### Dissemination

Trial results will be communicated to the scientific community via journals and national and international conferences.

## Discussion

The Hi-DoRi-3 is a phase 3 open-label, multicenter, randomized, non-inferiority clinical trial that aims to investigate the effectiveness of a high-dose rifampicin-containing regimen for the treatment of drug-sensitive TB. In this study, the effectiveness and safety of a regimen with a shortened and individualized treatment duration will be compared with the standard 6-month regimen for TB treatment. The three-drug intervention regimen will include high-dose rifampicin (30 mg/kg) with isoniazid and pyrazinamide, which will be administered until culture conversion, followed by 12-week administration of high-dose rifampicin and isoniazid.

In South Korea, the treatment success rate of TB is ~ 90%. While less than 1% of TB patients could not be cured, 5.3–25.2% of TB patients were lost to follow-up [23]. The standard 6-month regimen, comprising four drugs, has remained unchanged for almost 40 years [3]. To enhance compliance and adherence to TB treatment, simple, less toxic, and shorter regimens are needed. With the aim to shorten treatment duration in TB patients, 4-month fluoroquinolone-containing regimens were compared with the standard treatment [7–9]; however, non-inferiority of these regimens was not proven.

For the last ~ 40 years, recommendations for the maximal dose of rifampicin have been confined to 10 mg/kg or 600 mg per day [4, 17]. The peak concentration after ingestion of the currently recommended dose of rifampicin is considered to be well above the minimum inhibitory concentration of *M. tuberculosis* [13]. However, this dose is at the lower end of the dose–response curve, and the drug concentration in *M. tuberculosis* and at the site of infection has not been considered [13]. Increased rifampicin exposure led to higher bactericidal and sterilizing activity for TB according to several in vitro and in vivo studies [24–26]. In human studies, higher doses of rifampicin shortened the time to sputum culture conversion compared with the conventional rifampicin dose [12, 14, 27]. The rate of serious adverse events in patients receiving higher doses of rifampicin was comparable to that in patients receiving the conventional dose [16].

When rifapentine, a cyclopentyl derivate of rifampicin, was administered twice weekly with moxifloxacin for 2 months, followed by 2 months of moxifloxacin, ethambutol, rifampicin, and pyrazinamide, ~ 20% of patients had unfavorable outcomes, and this strategy was proven to be inferior to the standard regimen [8]. Fortunately, a recent study showed that daily administration of 1200 mg of rifapentine with moxifloxacin, isoniazid, and pyrazinamide could shorten the treatment duration by up to 4 months without non-inferiority [6]. In our trial, high-dose rifampicin, which is more affordable than rifapentine [28], will be tested as a means to shorten treatment duration. In addition, the total duration of treatment will be individualized according to the timing of culture conversion, which will reflect each patient’s disease severity and treatment response.

In conclusion, our study will inform on the feasibility of a treatment regimen using high-dose rifampicin with a shortened and individualized treatment duration for pulmonary TB.

### Trial status

Recruitment began at the first site in November 2020 and is expected to be completed by August 2025.

## Data Availability

The results of this trial will be disseminated only by presentation at academic meetings or publication in academic journals.

## Abbreviations

AFB: Acid-fast bacilli
CTCAE: Common Terminology Criteria for Adverse Event
e-CRF: Electronic case report form
DSMB: Data and Safety Monitoring Board
hCG: Human chorionic gonadotropin
mITT: Modified intention-to-treat
MRCC: Medical Research Collaborating Center
PP: Per protocol
REDCAP: Research Electronic Data Capture
TB: Tuberculosis
